## Abstract

**Background:**

In 2008 the World Health Organization (WHO) reported that South Africa had the highest tuberculosis (TB) incidence in the world. This high incidence rate is linked to a number of factors, including HIV co-infection and alcohol use disorders. The diagnosis and treatment package for TB and HIV co-infection is relatively well established in South Africa. However, because alcohol use disorders may present more insidiously, making it difficult to diagnose, those patients with active TB and misusing alcohol are not easily cured from TB. With this in mind, the primary purpose of this cluster randomized controlled trial is to provide screening for alcohol misuse and to test the efficacy of brief interventions in reducing alcohol intake in those patients with active TB found to be misusing alcohol in primary health care clinics in three provinces in South Africa.

**Methods/Design:**

Within each of the three selected health districts with the highest TB burden in South Africa, 14 primary health care clinics with the highest TB caseloads will be selected. Those agreeing to participate will be stratified according to TB treatment caseload and the type of facility (clinic or community health centre). Within strata from 14 primary care facilities, 7 will be randomly selected into intervention and 7 to control study clinics (42 clinics, 21 intervention clinics and 21 control clinics). At the clinic level systematic sampling will be used to recruit newly diagnosed TB patients. Those consenting will be screened for alcohol misuse using the AUDIT. Patients who screen positive for alcohol misuse over a 6-month period will be given either a brief intervention based on the Information-Motivation-Behavioural Skills (IMB) Model or an alcohol use health education leaflet.

A total sample size of 520 is expected.

**Discussion:**

The trial will evaluate the impact of alcohol screening and brief interventions for patients with active TB in primary care settings in South Africa. The findings will impact public health and will enable the health ministry to formulate policy related to comprehensive treatment for TB and alcohol misuse, which will result in reduction in alcohol use and ultimately improve the TB cure rates.

**Trial registration number:**

PACTR: PACTR201105000297151

## Background

The 2008 World Health Organization (WHO) Report found that South Africa had the highest tuberculosis (TB) incidence in the world, at over 5 times the average incidence rate found in the 22 high-burden countries. In 2006, South Africa with only 0.7% of the world's population had an estimated 28% of HIV positive adult TB cases reported globally. Over the last 5 years TB case notification has increased by a massive 81%, from 188 695 cases in 2001 to 341 165 cases in 2006. In 2006 KwaZulu-Natal, one of the nine provinces in South Africa, had the highest total TB caseload accounting for 31% of all TB cases nationally [1].This increase is mostly associated with the co-morbidity between HIV and TB. However, other factors, such as poverty and alcohol misuse is also associated with TB incidence. The role of alcohol misuse in increasing TB incidence has been under-studied within the South African context and has consequently not been adequately addressed in TB prevention efforts.

Excessive alcohol use has been causally linked to TB incidence. Two pathways are involved: the first is biological via weakening of the immune system, and the second is social via social exclusion and drift, resulting in about a threefold increased risk of TB [2]. Alcohol use was estimated to have been responsible for 939 000 disability-adjusted life-years lost in South Africa for TB and HIV/AIDS alone in 2004 (253 000 for women, 687 000 for men). This figure corresponds to 4.6% of the overall disease burden in South Africa (2.5% for women, 6.6% for men). These numbers show the potential for reducing alcohol-attributable infectious disease burden in South Africa, since cost-effective measures for reducing alcohol-attributable harm in developing societies exist and could be applied [2].

There are numerous studies cited in the literature that support the strong association between alcohol use, alcohol use disorders and TB [3-8]. Numerous studies show pathogenic impact of alcohol on the immune system causing susceptibility to TB among drinkers [4,7,9]. "Alcohol use strongly influences both the incidence and the outcome of the disease and was found to be linked to altered pharmacokinetics of medicines used in the treatment of TB, social marginalization and drift, higher rate of re-infection, higher rate of treatment defaults and development of drug-resistant forms of TB; about 10% of the TB cases globally were estimated to be attributable to alcohol" [3]. People that drink heavily show higher relapse rates, a higher probability of an unfavourable clinical course and a higher probability of experiencing the most destructive forms of TB. High prevalence of alcohol misuse in most population groups have been reported in South Africa. A household survey conducted in Mamre in the Western Cape Province (a community of approximately 5 000 people) found a positive association between TB and alcohol problems in the households [10].

Hazardous and/or harmful alcohol use is on the increase in developing/middle income countries including South Africa. Hazardous drinking is defined as a quantity or pattern of alcohol consumption that places patients at risk for adverse health events, while harmful drinking is defined as alcohol consumption that results in adverse events (e.g., physical or psychological harm) [11]. In South Africa more than 22% of men and women engage in hazardous or harmful drinking during weekends [12]. Among a primary health care outpatient sample of 600 rural South Africans 37.4% of men and 10.7% of women were found to be hazardous drinkers, and 9.2% of men and 0.3% of women meet criteria for probable alcohol dependence or harmful drinking as defined by the AUDIT [13]. Prevalence estimates range from 4% to 29% for hazardous drinking and from less than 1% to 10% for harmful drinking [11]. In a another multi-country study a prevalence of hazardous alcohol use of 18% (after non-drinkers and alcoholics had been excluded) was found among patients attending primary health care facilities in Australia, Bulgaria, Kenya, Mexico, Norway and the USA [14]. Similar prevalence rates of hazardous drinking in primary care outpatients were found in Nigeria (28.6%) [15] and 25% in Harare, Zimbabwe [16], and a low prevalence of above 1.7% alcohol dependency or harmful drinking in Nigeria [17].

In March 2006, in line with a WHO/AFRO decision of African Health Ministers, a TB Crisis Management Plan was launched by the Minister of Health in South Africa. The plan focused on 4 districts in South Africa which had a quarter of the national TB case load. These districts were: Amatole and Nelson Mandela Metro in the Eastern Cape Province, EThekwini Metro in KwaZulu-Natal Province, and the Johannesburg Metro in Gauteng Province. The mainstay of the plan was social mobilization to ensure that TB is de-stigmatized, that people seek treatment early, and that patients complete treatment [18].

### Screening and brief interventions for alcohol use disorders

Increasing emphasis has been placed on the detection and treatment of hazardous and harmful drinking disorders, particularly among patients who are seen in primary health care settings [11]. Screening instruments such as the Alcohol Use Disorders Identification Test (AUDIT), CAGE, and Screening and Brief Interventions (SBIs) have been found to be useful in detecting and treating alcohol use disorders in a number of settings [13,19,20]. The interventions are based on cognitive- behavioural interventions and motivational interviewing techniques and have been found to be effective and efficient in the treatment of alcohol use disorders in most chronic conditions. In previous studies screening and brief intervention for alcohol problems have been successfully implemented by nurses in demonstration projects in South Africa as part of a WHO strategy to expand screening and brief intervention for alcohol problems in developing countries funded by WHO and NIAAA [13,19]. Community health workers have been identified as strategic implementation agents for screening and brief intervention of alcohol problems in primary care in South Africa.

Whilst there have been studies conducted on screening for alcohol misuse and brief interventions producing favourable results, there is a dearth of scientific literature on evidence-based best practice methods to screen for alcohol misuse and brief interventions amongst individuals with active TB. Given the fact that in South Africa the target rate for TB cure has not been met, and the fact that alcohol use and misuse is known to be a causal factor in TB onset, there is an urgent need to conduct a cluster randomized control trial to evaluate SBIs for alcohol use disorders among TB patients. This should be perceived as a key intervention to improve the outcomes for TB treatment and control. The alcohol-related risk reduction intervention programme proposed in this study, will be based on a modified Information Motivation and Behavioural Skills (IMB) model of health promoting behaviours and alcohol risk reduction intervention to reduce hazardous and/or harmful alcohol consumption.

### Aim of the study

The aim of this study is to conduct a cluster randomized control trial to assess the effectiveness of SBI for alcohol use disorders among TB patients. Consenting patients who are starting TB treatment and screen for alcohol use risk are randomized, with the primary care clinic being the unit of randomization into one of two arms: The first arm being a Brief Intervention for alcohol misuse arm (treatment arm) and the second arm being the treatment as usual where patients receive an alcohol education leaflet (control arm).

#### Objectives

1. To screen for alcohol misuse among TB patients in the selected sites.

2. To implement Screening and Brief Interventions (SBI) among TB patients that screen positive for alcohol misuse.

3. To monitor and evaluate the treatment outcomes for both alcohol misuse and TB among TB patients.

4. To report on the outcome of the intervention (SBI) and make recommendations for future interventions for reduction in alcohol use.

## Methods/Design

### Setting

Three provinces, in South Africa, with the highest TB caseload will be selected for inclusion in the study. One district in each province (N = 3) with the highest TB caseloads will ultimately be included. These districts are Siyanda in Northern Cape Province, Nelson Mandela Metro in the Eastern Cape Province, and EThekwini in KwaZulu-Natal Province. Within each of these three study districts 14 primary health care facilities will be selected on the basis of the highest TB caseloads per clinic (N = 42). The type of health facility will be a primary health care clinic or community health centre. The study catchment areas within the study health districts and randomization procedures will enable broad coverage of major population groups.

### Design

In order to assess the effectiveness of the Screening and Brief Interventions (SBI) among participants newly diagnosed with TB and found to be misusing alcohol, a cluster randomized controlled trial design will be implemented. All new TB patients will be screened using the Alcohol Use Disorder Identification Test (AUDIT). TB patients who meet the cut-off for misusing alcohol both in the intervention and control arms will be reassessed after baseline assessment at time 2 (3 months following intervention) and time 3 (6 months following intervention). The intervention will comprise the following: personalized feedback on AUDIT results, a health education leaflet, simple advice and brief counselling about reducing excessive drinking, during one -20 minute- session. The trial will incorporate cluster randomization of primary health care facilities to avoid the risk of contamination.

#### Study hypotheses

• Individuals receiving the brief intervention will experience a greater change in mean number of AUDIT (alcohol risk) scores and mean number of heavy drinking days, compared with the individuals receiving a health education leaflet only (control group)

• Alcohol consumption (use and misuse) will be associated with anti-tuberculosis medication adherence and TB treatment outcomes.

### Principles for recruitment

#### Inclusion criteria

##### Primary Health Care Clinics

Clinics with a high TB case-load (based on statistics collected by the Department of Health) in each of the three study districts with a high burden of TB will be included in the study.

##### Patients with active TB

New tuberculosis treatment patients (i.e. those patients who have been initiated or have been on anti-TB treatment for less than one month), males and females, 18 years and above who visit the primary health care facility and who score 8 or more for men and 7 or more for women on the AUDIT questionnaire after screening will be included in this study. Some researchers found that brief interventions are effective even among excessive drinkers [21-23]. Therefore patients scoring high on the AUDIT are included in the study.

#### Exclusion criteria

##### Patients with active TB

New tuberculosis treatment patients under the age of 18 years will not be included. In addition those individuals 18 years and older scoring less than 8 for men and less than 7 for women on the AUDIT questionnaire will be excluded from the study. Women who are pregnant, patients already under treatment for alcohol misuse and patients who have symptoms of psychosis and who are mentally handicapped will be excluded.

#### Randomisation

Randomisation will be conducted using a secure remote randomization service. Within each district in each of the three provinces the 14 primary health clinics with the highest TB caseloads will be randomly assigned to the treatment and control arms, stratified by clinic type (clinic and community health centre) and TB case load. TB patients misusing alcohol will be randomized to either the treatment or control group. At clinic level all consecutive new TB patients will be systematically recruited over a period of six months.

#### Blinding

Participants (clinic staff members and TB patients) will not be blind to their intervention or delayed intervention status. However, to protect against information biases in the reporting of alcohol use and TB adherence behaviour, the data collection team who will assess the outcomes will be blind to the clinic's status as intervention or delayed intervention arm.

### Procedure

Universal screening of all new tuberculosis treatment patients will be used whereby all consecutive clients visiting the primary health care facility will be screened for alcohol problems and be offered a brief counselling intervention. A health care provider who identifies a new TB treatment patient (within one month on treatment) will inform the patient about the study and refers the patient for participation if interested. A research assistant will ask for permission/consent from patients attending the primary care facility to participate in the stage 1 of the study, i.e. screening or baseline assessment using the AUDIT questionnaire. This will take about 15 minutes. The research assistant will not be involved in delivering the brief counselling intervention. All participants undergo the initial assessment and the research assistant will score the results of the alcohol test section of the questionnaire. Tuberculosis patients who will score 8 or more for men and 7 or more for women on the AUDIT questionnaire after screening (risky drinkers) will then be approached by the research assistant for a second informed consent for enrolment in stage 2, the intervention study. For patients included in the study, the research assistant refers the patient to a clinic counsellor who carries out the intervention (experimental or control) for all the participants after which they will be followed up at 3 months and 6 months at the health facility, and assessments will be done by the research assistant. The experimental intervention includes a brief counselling intervention on alcohol risk reduction consisting of two sessions, the first immediately after alcohol screening and the second within a month thereafter. In the control condition the clinic counsellor provides an alcohol education leaflet, and after completion of the 6 months follow-up, the trained clinic counsellor will provide the delayed intervention of brief counselling intervention on alcohol risk reduction. At follow-up at least six individual attempts are made to contact patients by telephone and letter. Even if a contact was not successful at 3 months, further attempts will be made at 6 months. Sampling will occur throughout all hours of clinic operation over a 6 months period. Thirteen tuberculosis patients will be recruited from each primary health care facility (n = 13). Participants will receive Rand 60 (8.5 US$) transport reimbursement at 6-month follow-up (see Figure 1).

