#### Consent

Consent to participate will be obtained in a 2-stage process. Research assistants will initially ask for informed consent to conduct a health screen and collect basic information and check eligibility to take part. No identifiable information will be collected at this stage. Patients who have a positive score on the AUDIT (alcohol risk score), as applicable, will have the study explained to them verbally and in writing (using the patient information sheet). Informed consent will be obtained at this second stage which will include permission to give the contact details to the research staff, and participate in the experimental or control condition and follow up after 3 and 6 months by the research assistant.

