The training will comprise of four elements: orientation to the relevant practice, standardised PowerPoint presentation, tape recorded simulated consultations with trained actors and ongoing clinical supervision by experienced HSRC staff. The simulated consultations will be recorded and rated by two independent clinical assessors. The brief intervention counsellor will be assessed for adherence to the brief counselling protocol in addition to their behaviour and skills using a Behaviour Change Counselling Index. Assessors will submit the ratings, comments and supervision points for each consultation. This information will support clinical supervision and training until the brief intervention counsellor reaches a required standard of practice agreed by the assessors [32,33].

To help protect against counsellor drift, the brief intervention will be completely manualized and can be used to guide the counsellor through the session content. Site visits will be done bi-weekly by the project manager to offer support and supervision to the trained clinic based study fieldworkers. In terms of control around the quality and consistency of the implementation of the intervention, intervention counsellors will fill in a patient for each counselling session conducted. It includes sections on client's AUDIT score, stage of change, action and intervention plan, handing of action plan to client and comments. Intervention counsellors will be compensated with R20 (US$2.6) for each counselling session conducted and monitoring form completed. In addition, study fieldworkers will be able to report to their coordinators regarding any problems they may be having in implementing the brief interventions. Regular meetings between the researchers and the project managers will allow for any problems to be resolved timeously.

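### Patients enter after their clinic's arm is set, through referral by unblinded clinic staff, so randomising clinics does not by itself protect against differential recruitment

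*Protocol article*

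**What the plan says.** Under Randomisation, the 14 clinics in each district "will be randomly assigned to the treatment and control arms, stratified by clinic type (clinic and community health centre) and TB case load". The same section then says "At clinic level all consecutive new TB patients will be systematically recruited over a period of six months".

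Under Procedure, a clinic health care provider identifies each new TB treatment patient and "will inform the patient about the study and refers the patient for participation if interested". The next step belongs to someone else: "A research assistant will ask for permission/consent from patients attending the primary care facility to participate in the stage 1 of the study". The assistant scores the AUDIT, approaches those above the cut-off for a second consent and does not deliver the counselling. The counselling is described as "consisting of two sessions, the first immediately after alcohol screening and the second within a month thereafter".

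Under Blinding: "Participants (clinic staff members and TB patients) will not be blind to their intervention or delayed intervention status". The section adds that the team assessing outcomes will be blind to the clinic's arm.

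Under Consent, the second stage includes agreement to "participate in the experimental or control condition and follow up after 3 and 6 months by the research assistant".

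Under Counsellor training and intervention quality assurance: "Intervention counsellors will be compensated with R20 (US$2.6) for each counselling session conducted and monitoring form completed". These counsellors are existing lay counsellors and nurses of the study clinics.

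**The concern.** When clusters are randomised and their members recruited afterwards, randomisation balances the clusters in expectation. It does not balance the people recruited unless finding, inviting and enrolling them is independent of the arm. Here the first contact is made by a member of clinic staff who knows the arm, and referral depends on the patient's interest after that conversation. A provider in a counselling clinic may present the study differently, or to different patients, from a provider in a leaflet clinic. A patient who has learned what the clinic offers may also decide on that basis.

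At stake is the primary comparison. If one arm enrols more people who were going to cut down anyway, the between-arm difference in AUDIT change mixes the effect of counselling with the effect of who entered. Readiness to change is a plausible trait of this kind. It is absent from the baseline measures shared by both arms under Outcome Measures; it is assessed within the counselling and recorded on the intervention counsellors' form. The direction of any such bias is unknown in advance, and it cannot be undone once patients are enrolled.

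**Working it through.** **Step 1. Is the arm set before patients enter?** The order is implied rather than stated. Clinics are the allocated units, and the first counselling session follows screening at once, so a clinic's arm must be fixed before its patients are screened. One sentence under Randomisation says that TB patients misusing alcohol will be randomised. That conflicts with clinic allocation and should be reconciled.

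**Step 2. Who controls each step of entry?**

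| Step | Who acts | Blind to arm? |
|---|---|---|
| Patient identified, informed, referred | Clinic health care provider | No (Blinding) |
| Stage 1 consent, AUDIT, scoring | Research assistant | Outcome data collectors are stated to be blind |
| Eligibility | Numeric AUDIT cut-off: 8 (men), 7 (women) | Not a judgement |
| Second consent requested | Research assistant | As above |
| Second consent given or refused | Patient | Not blind; when the patient learns the arm is not stated |

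The first row is open to arm knowledge on the text itself. The last is open because nothing closes it.

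**Step 3. Can the analysis repair it?** The intention-to-treat sections cover all randomised clinics and all recruited patients, so they are conditional on entry. Taking account of the strata balances clinics by caseload and type. The weights under Analysis approach model dropout after entry. None acts on who was referred or who agreed.

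**Step 4. How large could it be?** The document gives no rate of selective referral, so the following is illustration only.

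- Inputs from Sample size calculation: AUDIT 12 against 10.6, a difference of 1.4; 80% power; 5% level (two-sided assumed); design effect 2; N = 452.
- No SD is stated, so 452 cannot be reproduced directly. The SD it implies is 1.4 × √(113/2) / (1.960 + 0.842) = 3.76, where 113 = 452/2/2 is the effective number per arm.
- Implied standard error of the difference: 1.4 / (1.960 + 0.842) = 0.50.
- Assumed bias = (between-arm difference in the share of patients ready to change) × (their extra fall in AUDIT, whatever the arm).
- Error rate with no true effect = P(Z > 1.96 − bias/0.50) + P(Z < −1.96 − bias/0.50).

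| Assumed share difference | Assumed extra fall | Bias (points) | Share of 1.4 | Error rate |
|---|---|---|---|---|
| 5 percentage points | 2 | 0.10 | 7% | 5.5% |
| 10 percentage points | 3 | 0.30 | 21% | 9.2% |
| 20 percentage points | 3 | 0.60 | 43% | 22.5% |
| 20 percentage points | 4 | 0.80 | 57% | 36% |

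A bias in the other direction costs power. At 0.30 points against the intervention, power is P(Z > 1.96 − (1.4 − 0.30)/0.50) = P(Z > −0.24), about 60% instead of 80%.

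Sensitivity to the SD, using the planned final sample of 468 (234 per arm) and SE = SD × √(2 × 2/234): a bias of 0.35 points gives an error rate of 11% at SD 3.76 (SE 0.492) and 7% at SD 6 (SE 0.784).

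**The case against.** The plan has real safeguards. A research assistant who does not deliver the intervention takes both consents and scores the AUDIT, eligibility is a numeric threshold, recruitment is meant to be consecutive, and outcome assessors are stated to be blind. Any recruitment depends on willingness, so referral of interested patients is in tension with universal screening rather than a flat contradiction of it. Control patients are offered the counselling after six months, which narrows the difference in what the arms offer. The primary outcome is a change from baseline, so a difference in starting AUDIT is partly handled. A condensed article may also leave recruitment logs to the full protocol.

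Most of this stands, and it limits the point. It does not remove it: a cut-off and a separate consent-taker act only on patients already referred, and change from baseline does not adjust for an unmeasured inclination to change. The assistant's blinding may also be hard to keep, since the assistant sends each enrolled patient to the clinic's counsellor.

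A reader might infer more than the text supports:

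- **That paid clinic staff take consent.** They do not; the research assistant does.
- **That patients give second consent knowing their arm.** The wording under Consent fits a neutral information sheet equally well, and Blinding does not say when patients learn their status.
- **That payment rewards enrolment in one arm only.** Payment is for sessions and forms, not referral. The document does not say that the referring provider is a paid counsellor, or that control counsellors go unpaid. Overlap is possible because nurses may be counsellors, so payment is at most a possible aggravating factor.

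**Conclusion.** The point holds in limited form. Entry follows allocation and passes through an unblinded clinic provider whose referral depends on the patient's interest. The document does not say that the condition is withheld until second consent and baseline are complete. Randomising clinics therefore does not by itself protect against differential recruitment, and the stated analysis cannot remove it. It would go too far to say that randomisation gives no protection: clinic-level factors are still balanced in expectation.

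The actual bias cannot be computed from the document. The 5.5% to 36% range is correct arithmetic on assumed inputs: a 5 to 20 percentage-point imbalance, a 2 to 4 point extra fall, a two-sided test and the standard error implied by the planned effect. Its low end is negligible. It shows only that, against a planned effect of 1.4 points, moderate selection would matter. Should be fixed; moderate confidence.

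**What to change.** 1. **Procedure.** Replace discretionary provider referral with an approach by the research assistant to every consecutive new TB treatment patient, found from the clinic's TB treatment list, with the same script in all 42 clinics. Reconcile this with the statement under Consent that no identifiable information is collected at the first stage, for example by logging counts only.
2. **Consent.** Use one identical, neutral information sheet and second consent in both arms. The counsellor discloses the clinic's condition only after second consent and all baseline measures are complete.
3. **Entry log.** Count patients identified, approached, screened, positive and consenting, by clinic and arm. Compare stage 1 AUDIT and sex between positives who declined and those who enrolled; both are known before second consent, so no new measurement is needed.
4. **Payment.** State that counsellor payment is not tied to enrolment, or make it the same per patient in both arms. If control counsellors are at present unpaid, R20 for one contact with each of 260 control patients (half of 520) is R5,200, about US$676 at the article's rate. The Procedure section gives intervention patients two sessions, so parity per patient would take R40 × 260 = R10,400, about US$1,352.

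The cost is a wording amendment, a changed script for assistants already in the clinics and a simple log. The main downside is that patients consent before learning which condition their clinic offers, which the ethics committee must accept. No extra patients are needed.
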